### Implementation {16c}

A research assistant or psychotherapist will communicate the allocation to patients and introduce them to either the intervention or the control condition.

## Assignment of interventions: blinding

### Who will be blinded {17a}

Not applicable. The nature of the study’s intervention does not allow blinding.

### Procedure for unblinding if needed {17b}

Not applicable. The nature of the study’s intervention does not allow blinding.

## Data collection and management

### Plans for assessment and collection of outcomes {18a}

In this study, training of assessors will be facilitated by the research team to ensure standardized administration of the study instruments. The study instruments encompass a comprehensive array of assessments. The used questionnaires comprise self-report instruments only, and participants will be invited to complete the questionnaires digitally, meaning that all values will be transferred immediately to our database to promote data quality. The quality of the assessment will be ensured by having all participants complete the questionnaires individually during the diagnostic sessions in a quiet room without any distractions. All of the study’s instruments were chosen based on satisfactory reliability and validity.

#### Primary outcome self-report questionnaires

The FTND [20], a ten-item scale with dichotomic items, is considered highly reliable and valid [50], *rtt* = 0.88, α = 0.61). The scores can range from 0 to 10, while scores from 0 to 2 indicate no/very weak tobacco dependence, scores.

The ASSIST [66] is an efficient measure due to its capability for the simultaneous assessment of multiple addictive substances and has undergone rigorous validation [29, 46, 66]. For tobacco consumption, concurrent validity of the original version of the ASSIST was indicated by significant correlations of substance-specific subscale scores of ASSIST and the scores in FTND (*r* = 0.85; [46]). Average test-retest reliability coefficients range from good to excellent depending on the substance class [66]. Reliability was proven good for tobacco (*α* = 0.83; [65]). Scores from 3–7 indicate moderate dependence, and scores of 8–10 indicate very high dependence.

The BDI-II [6] is a self-report questionnaire assessing the severity of depressive symptoms across 21 symptom areas that has good internal consistency (*α* = 0.90–0.93) and its reliability can be considered good (*rtt* = 0.78; [6]). The total score can range from 0 to 63; scores below 9 indicate no evidence of depression, 9–13 suggest minimal depression, 14–19 indicate mild depression, 20 or above suggest moderate depression, and scores of 29 or above suggest severe depression.

The BSCL [23] assesses an individual's perceived impairment due to 53 physical and psychological symptoms, consists of nine subscales, and has been evaluated in numerous studies. The authors report good internal consistencies ranging from 0.71 to 0.85 and test-retest reliabilities ranging from 0.68 to 0.91, depending on the subscale [23].

The short version of the WHO Quality of Life Questionnaire (WHOQOLBREF) assesses the dimensions of physical well-being, psychological well-being, social relationships, and environment, and is considered to have “good to excellent” psychometric properties [60], with internal consistencies ranging from 0.66 to 0.84 [71].

The WHO-5 is a psychometric tool used to assess an individual's overall well-being and mental health and consists of five 6-point items. The German version has good internal consistency (*α* = 0.92) and very good reliability (*rtt* = 0.87; [11]).

#### Primary outcome instruments targeting biomarkers

Carbon monoxide is assessed using a piCO™ Smokerlyzer® (Bedfont Scientific Ltd.). CO levels are objective markers of heavy smoking, and a value of 7.5 ppm in exhaled CO can be considered an appropriate cutoff to differentiate non-smokers from active smokers [2]. Cotinine is assessed using single rapid urine tests (nal von minden gmbH) with a cutoff of 200 ng/mL, which is a commonly used cutoff for detecting nicotine exposure for up to 5 days [34].

### Primary outcome measures measuring implicit processes

Approach biases towards smoking-related stimuli and non-smoking control stimuli are measured using the standard joystick AAT [53] as modified by Machulska et al. [42]. In this task, participants view various images on a computer screen, each slightly tilted either 3° to the left or to the right. Using a Logitech Extreme 3D joystick connected to the computer, participants are instructed to push images rotated to the right and pull images rotated to the left using the joystick. This action causes the images to either shrink or grow in size, depending on the direction of the arm movement. According to Rinck and Becker [53], an approach bias score for a particular picture category (e.g., smoking or control images) is determined by the difference in reaction times (measured in milliseconds, ms) between approach and avoidance movements. Approach biases are calculated for each of the picture categories and across each diagnostic session. A positive difference score indicates that the participant was quicker to approach than to avoid a particular stimulus category, signifying an approach bias. The task includes 50 smoke-related pictures and 50 non-smoking control pictures. Each picture will be presented once in push-away format and once in pull-closer format, respectively, resulting in 200 total trials.

#### Secondary measures: self-report questionnaires

The GSE measures generalized self-efficacy and has good reliability (*α* = 0.71–0.89; [33]). The unidimensional SESS measures smoking-related self-efficacy and consists of 9 items, demonstrating an internal consistency of *α* = 0.95 and test–retest reliability of *r* = 0.85 [32]. The FEVER measures stages of change and has good internal consistency, with Cronbach’s alpha ranging from 0.76 to 0.86 depending on the subscale [26]. For the SOC, a scale also measuring stages of change that varies from 0 (precontemplation) to 4 (maintenance), studies have reported a test–retest product-moment correlation of *r* = 0.78 [18]. The MTSS measures the motivation to quit smoking, and area under the receiver operating characteristics (ROC_AUC_) curves of the MTSS show good external validity (ROC_AUC_ = 0.64, [49]). The authors of the APOI report good internal consistency for depressive patients (*α* = 0.77). In addition, convergent validity was tested by analyzing correlations of the APOI with an established instrument and was proven to be adequate, *r* = 0.74 [57].

### Plans to promote participant retention and complete follow-up {18b}

Participants will be informed about the study’s objective and the importance of completing the treatment and the follow-up evaluation, emphasizing the potential personal benefits of the treatment. Patients will receive a telephone call prior to each follow-up assessment to remind them of the date and encourage adherence to the program.

### Data management {19}

Data entry will be performed under the supervision of the research staff. The data will be electronically stored on a secure research server provided by the University of Siegen.

### Confidentiality {27}

All the data will be collected and stored in a pseudonymized manner (i.e., with a subject code) on a secure, access-restricted research server provided by the University of Siegen. Only anonymized data will be published. Subsequent linking of individuals to their data can only be performed with a datasheet, which will be securely stored and destroyed after the study is completed (but no later than 10 years).

### Plans for collection, laboratory evaluation and storage of biological specimens for genetic or molecular analysis in this trial/future use {33}

Not applicable. Cotinine urine tests will be evaluated immediately after the urine sample is provided and disposed of after using self–diagnostic test strips.

## Statistical methods

### Statistical methods for primary and secondary outcomes {20a}

Treatment effects on the continuous primary outcomes (i.e., tobacco dependence, smoking intensity, mental health symptoms) will be tested by computing mixed 2 (condition) × 4 (time) analyses of variance (ANOVAs) for repeated measurements for each applied outcome variable. To reduce the likelihood of Type I errors due to multiple comparisons, the false discovery rate (FDR) will be controlled using the Benjamini-Hochberg procedure [7] across the primary outcome measures. In the case of potential violations of the sphericity assumption, the Greenhouse–Geisser method will be applied.

It will be examined whether the experimental condition leads to higher abstinence rates at post- and follow-up assessments using chi-squared tests.

Secondary and exploratory analyses testing for potential mediating variables will be conducted using regression analyses or structural equation modeling. Treatment effects on the AAT will be tested by computing mixed 2 (condition) × 4 (picture category) analyses of variance.

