### Objectives {7}

We expect a treatment effect of the intensified smoking cessation on variables regarding tobacco dependence severity, smoking behavior as well as mental health outcomes, as evidenced by a reduced nicotine dependence severity, reduced smoking intensity, a higher quality of life and subjective psychological well-being, and reduced perceived impairment of mental health symptoms and depressive symptoms in patients in the experimental condition receiving a smoking cessation intervention than in patients in the wait-list-control condition. These changes are expected to become apparent both in the short-term (i.e., post-treatment) as well as the long-term (i.e., 6 weeks and 6 months follow-up) when compared to the baseline measures.

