### Sample size {14}

To estimate the required sample size, an a priori power analysis was conducted using G*Power 3.1.9.7 [21]. The primary hypothesis will be tested using a 2 × 4 mixed-design repeated-measures ANOVA (with a power of 1 − *β* = 0.80 and a significance level of *α* = 0.05. This requires a sample size of approximately 62 participants in total, 31 per condition, to detect a moderate effect. No additional participants will be recruited to compensate for potential dropout; instead, the study design follows the intention-to-treat (ITT) principle and employs multiple imputation methods to address missing data. The decision to target a moderate effect size is driven by practical considerations to detect treatment effects that are both statistically significant and practically meaningful.

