### Methods for additional analyses (e.g., subgroup analyses) {20b}

Exploratory and demographic variables will be explored for potential associations with the group condition. If deemed appropriate, analyses regarding treatment effects on primary and secondary outcomes will be re-evaluated to control for potential confounding effects.

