### Adverse event reporting and harms {22}

Nicotine withdrawal associated with smoking cessation can, in some cases, lead to increased irritability, sleep disturbances, concentration problems, or heightened feelings of hunger. These withdrawal symptoms typically occur in the first few days after smoking cessation and usually subside within 2 to 3 weeks [16]. These topics will be discussed during the smoking cessation program (sessions 1 and 2), and management strategies will be collaboratively developed for and with the patients. For example, relaxation exercises to cope with irritability, adopting sleep hygiene practices, or providing alternatives to manage increased hunger, such as drinking water, consuming sugar-free gum, or engaging in physical activity, will be addressed. No additional mental strains beyond those typical of quitting smoking are expected as a result of the study. Patients who report adverse events will have the option to undergo evaluation by the research staff and a psychotherapist. Oversight of safety, protocol adherence, study quality, and ethical conduct will be the responsibility of the study coordination unit.

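### The 2 × 4 ANOVA treats the pre-randomisation baseline as an outcome level, so its interaction test does not locate the effect in time and loses power for the sustained benefit that the objectives predict

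*Protocol article*

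**What the plan says.** The protocol article's section on statistical methods {20a} states that treatment effects on the continuous primary outcomes "will be tested by computing mixed 2 (condition) × 4 (time) analyses of variance (ANOVAs) for repeated measurements for each applied outcome variable". The sample size section {14} names the same 2 × 4 mixed design for the primary hypothesis, with 80% power and "a significance level of *α* = 0.05", and arrives at a "sample size of approximately 62 participants in total, 31 per condition", "to detect a moderate effect". Outcomes {12} defines the four visits as baseline (t0), post-treatment (t1), 6-week follow-up (t2) and 6-month follow-up (t3). The participant timeline {13} places all baseline measures before random assignment.

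Objectives {7} expects the changes to appear "both in the short-term (i.e., post-treatment) as well as the long-term (i.e., 6 weeks and 6 months follow-up) when compared to the baseline measures".

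Three passages bear on adjustment. The section on comparators {6b} puts dummy variables for additional treatments into the ANOVAs. The missing-data section {20c} puts baseline scores into the imputation model. The section on additional analyses {20b} adds: "If deemed appropriate, analyses regarding treatment effects on primary and secondary outcomes will be re-evaluated to control for potential confounding effects". None of them puts the baseline value of the outcome into the analysis model. Tests at particular visits are named only for abstinence, by chi-squared tests.

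**The concern.** The objective concerns timing and persistence, whereas the named test is an omnibus one. A significant condition-by-time F says that the profile of arm differences over t0 to t3 is not flat. That can come from a benefit at t1 only, a benefit at t3 only, a sustained benefit, or a worsening at one visit. Taken alone, it supports neither the short-term nor the long-term claim.

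The second cost is efficiency. Randomisation makes the expected arm difference at t0 zero, so baseline carries no treatment effect. It is most useful as a covariate. As a fourth outcome level, its noise enters the comparison and the signal is spread over three degrees of freedom. With 62 participants and no allowance for dropout, there is little power to spare.

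For the mental health scales, t1 needs care in reading. Table 1 places the cessation phase in sessions 3 and 4. At two sessions a week that is week 2, and t1 is at week 3. The harms section {22} says withdrawal symptoms "usually subside within 2 to 3 weeks". A temporary worsening at t1 would also feed a non-directional interaction.

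**Working it through.** **Inputs from the protocol.** 31 per arm, 1:1 allocation, α = 0.05, power 0.80, four visits including baseline, a sustained effect as predicted in Objectives {7}.

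**Assumptions (not in the protocol).** Standardised difference d = 0.5 at t1, t2 and t3 and 0 at t0. Equal correlation ρ between visits (compound symmetry), with ρ = 0.3, 0.5, 0.7. No dropout, no additional-treatment covariates.

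**Step 1: the plan's own figure.** The effect is called moderate without a number, so take f = 0.25. For the condition-by-time interaction, with the effect size as in SPSS, λ = f²(N − 2)(4 − 1) = 0.0625 × 60 × 3 = 11.25 on F(3, 180). Power is 0.804, and N = 62 is reproduced. The match is not unique. G*Power's default option gives 24 at f = 0.25 and ρ = 0.5, but also 62 at f = 0.15 and ρ = 0.5. The between-arm test gives 62 at f = 0.25 and ρ = 0.3. The interaction is the natural reading.

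**Step 2: timing.** With mean arm differences δ over t0 to t3, λ = (31/2) × Σ(δ − δ̄)² / (1 − ρ). The sum of squares is 0.75d² for the sustained pattern (0, d, d, d), for t1 only (0, d, 0, 0) and for t3 only (0, 0, 0, d). The three are equally likely to give significance. At d = 0.7 and ρ = 0.5, λ = 15.5 × 0.75 × 0.49 / 0.5 = 11.39 and power is 0.81 in each case.

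**Step 3: power for a sustained d = 0.5.**

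- *Interaction.* At ρ = 0.5, λ = 15.5 × 0.75 × 0.25 / 0.5 = 5.81 on F(3, 180), power 0.49.
- *Baseline-adjusted mean of t1 to t3.* Residual variance (1 + 2ρ)/3 − ρ² = 0.667 − 0.25 = 0.417. λ = 15.5 × 0.25 / 0.417 = 9.3 on F(1, 59), power 0.85.
- *Joint baseline-adjusted test of t1 to t3.* λ = 15.5 × δ′S⁻¹δ, where S has diagonal 1 − ρ² and off-diagonal ρ − ρ². For equal differences λ is again 9.3, now on F(3, 57), power 0.69.
- *Main effect of condition in the ANOVA.* Averaging in t0 shrinks the difference to 0.75 × 0.5 = 0.375, with variance (1 + 3ρ)/4 = 0.625. λ = 15.5 × 0.1406 / 0.625 = 3.49, power 0.45. This term is no remedy.

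| Test | ρ = 0.3 | ρ = 0.5 | ρ = 0.7 |
|---|---|---|---|
| Interaction, 3 df | 0.36 | 0.49 | 0.74 |
| Adjusted mean of t1–t3, 1 df | 0.83 | 0.85 | 0.94 |
| Joint adjusted test, 3 df | 0.66 | 0.69 | 0.83 |
| Adjusted difference at one prespecified visit | 0.53 | 0.61 | 0.77 |
| d detectable with 80% power, interaction | 0.82 | 0.69 | 0.54 |
| d detectable with 80% power, adjusted mean | 0.48 | 0.47 | 0.40 |

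Simulation with the Greenhouse–Geisser correction gives 0.49 and 0.85 at ρ = 0.5. With a correlation that decays from 0.75 at lag 1, the interaction has 0.55 and the adjusted mean 0.82.

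**Step 4: a fading effect (0.5, 0.25, 0 at t1, t2, t3; ρ = 0.5).** Interaction: λ = 5.33, power 0.46. Adjusted mean: difference 0.25, λ = 15.5 × 0.0625 / 0.417 = 2.33, power 0.32. Joint adjusted test: λ = 6.2, power 0.50.

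**The case against.** The plan is consistent with itself: the test in {20a} is the one that {14} sizes, and 62 can be reproduced at 80% power. A mixed ANOVA with baseline as a level is a valid randomised comparison, and d = 0.5 is an assumption made here. All of that stands. The point concerns fit to the objective and efficiency, not validity.

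A reader might infer that the analysis cannot show short- versus long-term effects at all. The protocol does not support that. The limit is a property of the omnibus F. The fitted model still gives visit means, follow-up contrasts may stand in an analysis plan that is not shown, and abstinence already has tests by visit.

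A reader might also infer from {20b} that all covariate adjustment waits on observed imbalance. Section {6b} contradicts this, since it fixes the additional-treatment dummies in advance. Only the baseline outcome is missing from the model.

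Nor does the t1 withdrawal period justify taking post-treatment out of the confirmatory mental health test. The objectives predict benefit there too, and {22} describes symptoms as typically arising in the first days and then usually subsiding. A contrast restricted to t2 and t3 would drop a stated hypothesis. Its power for a sustained effect at ρ = 0.5 would be 0.78, not 0.85.

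Two further objections hold. The averaged contrast does not itself separate short- from long-term effects, so the visit differences must do that. Its advantage also depends on the pattern and on ρ. The test-retest values in {18a} (0.88 for the FTND, 0.78 for the BDI-II, 0.87 for the WHO-5) are high, although correlations over six months with treatment are probably lower. At ρ = 0.8 the interaction already has 0.90 and a single adjusted visit gains nothing, though the adjusted mean still reaches 0.98.

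**Conclusion.** The concern holds for the seven continuous primary outcomes. The named test uses a pre-randomisation measurement as an outcome, omits it as a covariate, and does not by itself answer when the arms differ. For the sustained effect in the objectives, the loss against the adjusted mean is 0.47, 0.36 and 0.20 in power at ρ = 0.3, 0.5 and 0.7 (0.83 − 0.36, 0.85 − 0.49, 0.94 − 0.74). Even a joint adjusted test with the same 3 df gains 0.30, 0.20 and 0.09. These sizes rest on d = 0.5, compound symmetry and complete data. The direction also holds under the decaying correlation that was tried. It reverses for the averaged contrast, but not for the joint test, under the fading pattern in Step 4. This should be changed, but it does not invalidate the trial.

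**What to change.** For each continuous primary outcome, fit a linear mixed model to t1, t2 and t3 with the baseline value as covariate, plus condition, visit and condition-by-visit.

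Prespecify one baseline-adjusted condition test per outcome as the p-value that enters the Benjamini-Hochberg procedure. The average over t1 to t3 matches the sustained effect in the objectives. The joint 3-df test is the safer choice if fading is a concern. The choice must be made before outcome data are examined.

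Report baseline-adjusted differences with 95% confidence intervals at t1, t2 and t3 for all these outcomes, mental health at t1 included. Interpret the t1 mental health difference with the withdrawal period of {22} in view. Rest statements about short- and long-term benefit on these visit differences.

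The cost is a change of wording and slightly more analysis work. No additional measurement is needed, since baseline is already collected. The price is lower power for the averaged contrast when the effect fades: 0.32 against 0.46 for the ANOVA in the example above, where the joint test has 0.50.

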### Eligibility criteria {10}

Participants must be at least 18 years old and exhibit harmful use of tobacco (F17.1 according to the ICD-10; [47]) or tobacco dependence (F17.2 according to the ICD-10) while also fulfilling the criteria for a treatment-relevant primary mental disorder. An exclusion criterion is acute suicidality, as well as the presence of an acute psychotic episode or the use of certain medications (e.g., neuroleptics such as Clozapine), where unmonitored cessation without a psychiatrist’s oversight may pose significant risks. The smoking intervention will be performed by trained clinical psychologists, while all psychotherapeutic consultations will be performed by trained psychological psychotherapists. If additional substance use disorders are present, treatment of these disorders is prioritized in accordance with German clinical guidelines [62] and ethical standards, particularly when inpatient treatment is indicated. Smoking cessation is then offered as an adjunctive treatment once the primary substance-related condition is overcome. This approach ensures appropriate care and participant safety.

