### Outcomes {12}

Primary outcomes include severity of tobacco dependence, smoking status, and mental health symptoms. All measures will be assessed at baseline (diagnostic session; *t*_0_), post (*t*_1_; *t*_0_ + 3 weeks), at follow-up assessment 1 (*t*_2_; *t*_1_ + 6 weeks), and at follow-up 2 (*t*_3_; *t*_1_ + 6 months).

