#### Primary outcomes targeting smoking behavior

Changes in tobacco dependency over time are operationalized as follows:Mean score changes in the"Fagerström Test for Nicotine Dependence"[20],German version: [9].Mean score changes in the “Alcohol, Smoking, and Substance Involvement Screening Test” (ASSIST) subscale for tobacco [58].Mean score changes in the measured carbon monoxide (CO) level in exhaled breath using the Smokerlyzer®, additionally assessed during each session of the intervention.

Changes in smoking status over time are operationalized as follows:d.Changes in the proportion of positive versus negative results in self-administered urine tests measuring cotinine content, using a dichotomous outcome (positive/negative; cutoff 200 ng/ml; for an overview, see [8]).

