### Participant timeline {13}

Smoking patients who have had three psychotherapeutic consultations at the Psychotherapeutic Outpatient Center of the University of Siegen will be informed about the option of participation in the current study. Interested participants will be contacted by the study team and undergo a telephone interview to determine eligibility and fulfillment of the inclusion criteria (*− t*_1_). Following telephone screening for a duration of 10–30 min, patients will be invited to the first smoking cessation session, during which informed consent will be obtained and psychological symptoms will be assessed within the course of a diagnostic session (baseline, *t*_*0*_). After the diagnostic session, during which all baseline measures will be assessed, patients will be randomly assigned either to the experimental group or the passive control group. The experimental condition will receive a 6-step smoking cessation program and additional access to a smartphone-based self-help application. The duration of the intervention will be three weeks. Afterwards, patients will be invited again to assess all measures of interest (*t*_1_). Six weeks (*t*_2_) and 6 months (*t*_3_) after completion, patients will be invited once again for follow-up assessments. The participants’ timelines and data assessment points are shown in Table 2..

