### Recruitment {15}

Participants will be recruited among individuals identified as regular smokers who previously had up to three psychotherapeutic consultations in the outpatient psychotherapeutic clinic at the University of Siegen. If the inclusion rate does not meet the requirements, additional advertisements to enhance participation in this project will be installed by the research team. If necessary, the planned duration of the enrollment period of 1 year will be extended.

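### The planned abstinence comparison ignores the baseline cotinine strip, so any participant already below 200 ng/ml at entry could count as abstinent without changing; the effect may be small

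*Protocol article*

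**What the plan says.** **Who enters.** Under Eligibility criteria {10}, participants must "exhibit harmful use of tobacco (F17.1 according to the ICD-10; [47]) or tobacco dependence (F17.2 according to the ICD-10"), alongside a primary mental disorder. Participant timeline {13} has candidates "undergo a telephone interview to determine eligibility and fulfillment of the inclusion criteria", which happens before any urine sample. Recruitment {15} draws on "individuals identified as regular smokers". None of these sections sets a cotinine value, a carbon monoxide (CO) value or a minimum daily consumption.

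**What is measured.** Under Primary outcomes targeting smoking behavior, smoking status is "Changes in the proportion of positive versus negative results in self-administered urine tests measuring cotinine content", "using a dichotomous outcome (positive/negative; cutoff 200 ng/ml". Outcomes {12} states that "All measures will be assessed at baseline" and at the three later visits. Participant timeline {13} places randomisation after the baseline session, so a strip result exists before allocation.

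**How it is analysed.** Statistical methods {20a} sends the continuous primary outcomes to a 2 × 4 mixed ANOVA. For the binary outcome it says: "It will be examined whether the experimental condition leads to higher abstinence rates at post- and follow-up assessments using chi-squared tests". It does not mention the baseline strip, and the protocol does not define abstinence.

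**The concern.** Entry is decided by diagnosis and interview, while the binary outcome is apparently decided by a biochemical cutoff. Harmful use (F17.1) does not require dependence, so the two need not coincide in every participant. Someone below 200 ng/ml at t0 cannot move from positive to negative. If that person goes on smoking in the same way, the strip stays negative and the person is counted as abstinent at t1, t2 and t3, in whichever arm.

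The outcome section describes a change in proportions, and the ANOVAs carry the baseline value as one of their four time points. The binary primary outcome alone is compared only after baseline. At stake are the abstinence rates that will be reported, which would be too high in both arms, and the power of a comparison with only 31 participants per arm.

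**Working it through.** **Is abstinence the strip result?** {20a} assigns the continuous primary outcomes to ANOVA. Of the eight primary measures (FTND, ASSIST, CO, cotinine, WHO-5, WHOQOL-BREF, BSCL, BDI-II) only cotinine is dichotomous. CO has a cutoff of 7.5 ppm in the section on biomarkers but is listed as an outcome only through mean change. The chi-squared tests therefore most likely use the strip. This is an inference.

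**The plan's own figure.** The protocol gives no abstinence rates and no sample size for this comparison. Its total of 62 belongs to the ANOVA. It reproduces for the group-by-time interaction if the moderate effect is taken as f = 0.25 (assumed) with the SPSS-style effect-size option in G*Power: λ = f²(N − 2)(m − 1) = 0.0625 × 60 × 3 = 11.25, with 3 and 180 degrees of freedom, gives power 0.804. The point made here does not affect that figure.

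**Dilution.** Inputs:
- n = 31 per arm and α = 0.05, from Sample size {14}.
- q, the share negative at t0: not in the documents; 0 to 20% shown.
- p, the true quit rate among baseline-positive participants: not in the documents; 35% (intervention) and 10% (control) assumed.
- Baseline-negative participants are assumed to stay negative throughout.

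Observed rate = q + (1 − q)p, so each arm's rate rises by q(1 − p).

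Observed difference = (1 − q)(0.35 − 0.10).

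Example at q = 10%: 0.10 + 0.90 × 0.35 = 41.5% and 0.10 + 0.90 × 0.10 = 19.0%. The difference is 22.5 points instead of 25, and the ratio is 41.5/19.0 = 2.2 instead of 3.5.

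Power comes from exact binomial enumeration of the uncorrected Pearson chi-squared test at two-sided 0.05. The restricted column uses 31(1 − q) per arm, rounded, with 35% v 10%.

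| q | Observed rates | Risk ratio | Power, all 31 per arm | n per arm, t0-positive only | Power, restricted |
|---|---|---|---|---|---|
| 0 | 35.0% v 10.0% | 3.5 | 0.680 | 31 | 0.680 |
| 1% | 35.7% v 10.9% | 3.3 | 0.659 | 31 | 0.680 |
| 2% | 36.3% v 11.8% | 3.1 | 0.638 | 30 | 0.661 |
| 3% | 37.0% v 12.7% | 2.9 | 0.618 | 30 | 0.661 |
| 5% | 38.3% v 14.5% | 2.6 | 0.581 | 29 | 0.642 |
| 10% | 41.5% v 19.0% | 2.2 | 0.495 | 28 | 0.625 |
| 20% | 48.0% v 28.0% | 1.7 | 0.374 | 25 | 0.601 |

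The number wrongly counted per arm is about 31q: 0.3 to 0.9 at q = 1 to 3%, 3.1 at 10% and 6.2 at 20%.

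Other assumed quit rates give the same pattern. With 40% v 10% and a two-proportion power formula, power is 0.79 at q = 0. At q = 10% it is 0.63 on all participants against 0.75 restricted.

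**The case against.** The strongest reply is that q is probably close to zero. The trial recruits regular smokers who also carry an F17 diagnosis, and the biomarker section says that the strip picks up exposure for up to 5 days. Such a person would be expected to test positive at t0. A reader might infer from the F17.1 criterion that a substantial group of light smokers will enter below the cutoff; nothing in the documents supports that. The rows for 10% and 20% are illustrations, and the rows for 1 to 3% fit the recruitment text better. This objection stands and sets the size of the point.

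A second reply is that the protocol never equates abstinence with a negative strip. That is correct, and a condensed article may leave the full definition elsewhere. But what the article does state is a comparison at post and follow-up with no use of a baseline result that is already collected.

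Third, comparing post-baseline proportions between randomised arms is a valid test. This also stands. A reader might infer that the comparison is biased in favour of treatment or inflates type I error. It does neither: baseline precedes allocation, so t0-negative participants are balanced in expectation, and the dilution runs toward the null. Nor is chance imbalance in their numbers a further harm, since the power figures already contain it.

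Finally, Methods for additional analyses {20b} allows re-analysis to control for confounding. It sets no rule for baseline cotinine, so it does not settle the matter.

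**Conclusion.** The point holds in a limited form. If abstinence means a negative strip, the stated analysis counts any t0-negative participant who goes on smoking unchanged as abstinent. This overstates abstinence in both arms, shrinks the risk difference by the factor (1 − q) and costs power. The test remains valid.

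The size depends on q, which the documents do not give. Under the assumed 35% v 10%, power falls by 2 to 6 percentage points at q = 1 to 3%, by about 10 at 5% and by about 31 at 20%. Restriction to t0-positive participants recovers part of this at every q above zero.

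The conclusion rests on three assumptions: the inferred definition of abstinence, the assumed quit rates, and t0-negative participants staying negative. The outcome is one of eight primary measures, and the sample size was not set on it. Severity is minor to moderate.

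**What to change.** In Statistical methods {20a}:

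- Define abstinence at a visit as a negative urine cotinine test at the stated cutoff.
- Make the between-arm comparison at t1, t2 and t3 among participants with a positive test at t0. Because t0 precedes randomisation, this restriction keeps the randomised comparison intact.
- Report the number of t0-negative participants by arm.
- Give the full-sample comparison as a sensitivity analysis.
- Keep t0-negative participants in all continuous analyses.

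The cost is a few sentences of analysis text. No new data or visits are needed, because the t0 strip is already planned. The downside is that a few participants leave the main abstinence analysis; if none is negative at t0, the result is unchanged. Data collection runs to April 2027 according to Trial status, so the rule can be fixed before analysis.
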